### Statistical Analysis

For the statistical analyses, repeated measures analysis of variance (ANOVA) and hierarchical linear models (HLMs) will be used. A 4 × 2 mixed ANOVA (primary outcome as dependent variable) with *Time* (pre vs. post vs. follow-up 1 vs. follow-up 2) as the within-subjects factor and *Group* (experimental vs. control group) as the between-subject factor will be conducted to investigate an interaction between time and group. In order to test specific effects, *post-hoc* tests will be employed. A HLM will be formulated to investigate time-dependent changes and group differences in task performance across stimulation sessions. A *p* < 0.05 will be considered statistically significant. Analysis will be conducted in *R* (121).

For the eye-tracking data, analysis of fixation duration and pupil dilation will be done in Tobii Studio 3.4.5 (107) following the preprocessing pipeline of other studies using eye-tracking to investigate emotion recognition and social cognition in adolescents with ASD [for the ERT (17) and for the MASC (106)]. These results in a fixation duration on the specified area of interest (AOI) and a measure of average pupil dilation per video. Further analysis regarding pre–post comparisons of AOIs and pupil dilation will be done in *R* (121) using linear models.

For the EEG data, we will employ the *MNE* library (122) written in *Python* (123) to execute data pre-processing, segmentation, and frequency and connectivity analyses. The raw EEG data of each participant will be segmented into epochs of 2 s. A multi-taper method with adaptive weights will be applied to each epoch to obtain power spectral density (PSD) values in each frequency band of interest. Frequency bands of interest will be delta (0.5–4 Hz), theta (4–8 Hz), and alpha (8–12 Hz). Subsequently, PSD values in each frequency band will be averaged across epochs separately for each participant, measurement occasion, and experimental condition.

Basic fMRI processing will be conducted according to (124) using Statistical Parametric Mapping [SPM; (125)]. To counteract the expected high level of in-scanner motion, PESTICA/SLOMOCO (126, 127) and the BrainWavelet toolbox (128) will be used for additional movement and artifact correction. Spatial normalization will be performed to a custom template created using the CerebroMatic toolbox (129) to avoid implausible deformation to match the usual standard adult brain. Subject-level analysis will be conducted using the general linear model in SPM. The FHA task will be modeled according to (118, 130). The ERTs will be modeled as block designs with a single condition. For the morphing variant, the reaction times will be included as a parametric modulator to uncover the possible influence of the subjective strength of the perceived emotion. The RS data will be analyzed by means of seed-based functional connectivity. Since the ERTs constitute newly implemented paradigms, interesting regions of their baseline activation will be used as seeds here. Nuisance regressors for the linear models will be derived *via* the CompCor (131) and Friston-24 (132) approaches with an additional bandpass applied to the RS data. Group-level analyses of fMRI data will be conducted using the Flexible Factorial module in SPM. The time-by-treatment interaction effects will be tested at *p* < 0.05 family-wise error corrected at the peak level and with a primary threshold of *p* < 0.001 uncorrected at the cluster level.

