#### Sample Size Calculations

Power analysis was done with G^*^Power version 3.1.9.2 (82) to detect a difference in the primary outcome [SRS, (83)] calculating repeated measures ANOVA considering an effect size *f* of 0.25, a power of 80%, and an α of 0.05. Previous studies in children with ASD have shown larger effect sizes for tDCS (63). A sample size of 20 participants (*N* = 20) will be necessary to report medium effect sizes on the primary outcome. Analyses of secondary outcomes were not included in the power analysis and therefore considered underpowered.

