#### Randomization

A total of 20 male participants will be included. To balance the experimental and control group with respect to comorbidities, all participants will be stratified into one of three subgroups based on their clinical presentation: subgroup A for participants without comorbidity, subgroup B for participants with depression as primary comorbidity, and subgroup C for participants with ADHD and/or conduct disorder as primary comorbidity. After subgroup stratification, the participants will be randomly allocated to the active condition or the sham condition by assigning a code to each participant. To ensure a quick study start for the participants after enrollment, a block randomization design will be used.

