### Outcomes

The primary outcome will be a reduction in ASD symptoms from baseline in the experimental group compared to the sham group. ASD symptoms will be quantified by the raw score of the German version of the SRS (83) assessed by the primary caregiver.

The secondary outcomes will be increased social cognition and emotion recognition quantified by the raw scores of the MASC (105) as well as correct classifications in the ERT and the FEFA 2 (120). Regarding gaze behavior, longer fixation duration on the eyes and increased pupil dilation will be the outcomes on the MASC and ERT. Outcomes on participants and caregiver ratings will be a decrease in ASD symptoms measured with the ATEC (95) and SCQ (96) and an increase in empathy and emotion regulation abilities measured with the ERQ (97), IECA (98), BES (99), GEM (100), and ERC (101). Neurophysiological activity will be measured at baseline and after the intervention using resting-state EEG and fMRI to measure changes in functional connectivity and electrical activity in the brain. We expect an increased resting-state alpha-power, a decrease in the other frequency bands, and an increased connectivity within the ToM network and DMN. An increased regional activation in key areas of the SBN will be the outcomes during the FHA and ERT.

The exploratory outcomes will include participant and caregiver ratings on comorbid symptoms of ASD using the DISYPS III (102). The brain activation in regions involved in emotion recognition processes and cognitive empathy during emotion recognition with the ERT during fMRI will also be examined exploratorily.

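### The primary 4 × 2 ANOVA uses the baseline SRS as a level of Time rather than as a covariate: a valid test, but less precise than a baseline-adjusted one unless the pre-post correlation is very high

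*Protocol article*

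**What the plan says.** The Outcomes section defines the target as a between-arm comparison of change: "The primary outcome will be a reduction in ASD symptoms from baseline in the experimental group compared to the sham group". The measure is a single scale: "ASD symptoms will be quantified by the raw score of the German version of the SRS (83) assessed by the primary caregiver".

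The Statistical Analysis section gives the primary model: "A 4 × 2 mixed ANOVA (primary outcome as dependent variable) with *Time* (pre vs. post vs. follow-up 1 vs. follow-up 2") as the within-subject factor and Group as the between-subject factor. It "will be conducted to investigate an interaction between time and group". Individual effects are left open: "In order to test specific effects, *post-hoc* tests will be employed". No baseline covariate is named for the SRS. The hierarchical linear model in that section is for task performance across stimulation sessions, and the linear models are for gaze and pupil data, so neither applies to the primary outcome.

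The Randomization section stratifies on comorbidity: "To balance the experimental and control group with respect to comorbidities, all participants will be stratified into one of three subgroups". SRS severity is not a stratification factor. The caption to Figure 1 places the baseline measures in the first week, ahead of randomisation and the sessions.

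**The concern.** A value taken before randomisation cannot be affected by treatment. Entering it as a response lets the two arms have different true baseline means and compares raw changes, which fixes the coefficient on baseline at 1. Under equal variances the best coefficient is the pre-post correlation, which is below 1. A coefficient of 1 over-corrects: an arm that happens to start higher tends to show the larger fall, whatever the treatment does.

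The cost is a larger error variance for the primary comparison. That matters in a trial of 20 whose secondary outcomes the article itself calls underpowered. The article fixes the dependent variable, the factors, their levels and the test, so this is a stated choice and not a detail left to an analysis plan.

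**Working it through.** **The plan's own figure.** The Sample Size Calculations section reports "calculating repeated measures ANOVA considering an effect size *f* of 0.25, a power of 80%, and an α of 0.05" and concludes "A sample size of 20 participants (*N* = 20) will be necessary to report medium effect sizes on the primary outcome". It gives neither the correlation nor the number of measurements. For a two-group, four-visit interaction the noncentrality is λ = f²·N·m/(1 − ρ) = 0.0625 × 20 × 4/(1 − ρ) = 5/(1 − ρ), on 3 and 54 df:

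- ρ = 0.5: λ = 10, power 72.7% (N = 24 would give 81.6%).
- ρ = 0.6: λ = 12.5, power 82.7%.
- Power reaches 80% at N = 20 from ρ of about 0.57.

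N = 20 is therefore neither confirmed nor refuted.

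**Assumptions for the comparison.** Unit SD, correlation ρ between all visits (compound symmetry) and 10 per arm (the allocation ratio is not stated). The effect is zero at baseline and d at all three later visits. With arm differences (0, d, d, d) the mean squared interaction effect is [(3d/8)² + 3(d/8)²]/4 = 3d²/64. Setting this to 0.25² gives d = 1.155 SD.

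**Variances for the mean of the three post-baseline visits.**

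- Change from baseline: (1 + 2ρ)/3 + 1 − 2ρ, t test on 18 df.
- Baseline-adjusted: (1 + 2ρ)/3 − ρ², t test on 17 df, with variance inflated by 1 + 1/17 for the estimated slope.

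**Worked at ρ = 0.5, d = 1.155.**

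- Change: variance 0.667, standard error √(0.667 × 2/10) = 0.365, noncentrality 1.155/0.365 = 3.16, power 85%.
- Adjusted: variance 0.417 (37% lower), 0.441 after inflation, standard error 0.297, noncentrality 3.89, power 95%.

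**Worked at ρ = 0.6, d = 0.8.**

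- Change: 0.8/√(0.533 × 0.2) = 2.45, power 64%.
- Adjusted: 0.8/√(0.373 × 1.059 × 0.2) = 2.84, power 76%.

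| ρ | Change variance | Adjusted variance | Power at 1.155 SD | Power at 0.8 SD |
|---|---|---|---|---|
| 0.3 | 0.933 | 0.443 | 71% → 94% | 42% → 69% |
| 0.5 | 0.667 | 0.417 | 85% → 95% | 55% → 72% |
| 0.6 | 0.533 | 0.373 | 92% → 97% | 64% → 76% |
| 0.7 | 0.400 | 0.310 | 97% → 99% | 76% → 84% |
| 0.8 | 0.267 | 0.227 | 99.7% → 99.8% | 91% → 93% |

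For a single post-baseline visit the variances are 2(1 − ρ) and 1 − ρ². At 1.155 SD power goes from 69% to 78% at ρ = 0.5, 78% to 84% at 0.6 and 88% to 91% at 0.7. For a single visit, if the change comparison has 80% power, adjustment gives 81.5% at ρ = 0.8 and 79% at ρ = 0.9, so the lost degree of freedom eventually outweighs the gain.

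**Simulation check.** In 20,000 trials per setting at 1.155 SD, power for the planned interaction, the post-mean change and the post-mean adjusted contrast was 72%, 85% and 95% at ρ = 0.5, and 83%, 92% and 97% at ρ = 0.6. Under no effect, the planned interaction rejected in 4.9% to 5.4% of 5,000 trials per setting for ρ from 0.3 to 0.9.

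**Chance imbalance.** The standard deviation of the baseline difference is √(2/10) = 0.447 SD, so a difference above 0.5 SD in either direction has probability P(|Z| > 0.5/0.447) = 26%. A 0.5 SD difference shifts the change-score estimate by (1 − ρ) × 0.5, which is 0.25, 0.15 and 0.10 SD at ρ = 0.5, 0.7 and 0.8. Adjustment removes this shift.

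**The case against.** Nothing in the article is contradictory here. The power calculation, the outcome and the model all speak of repeated measures and change from baseline. The planned test holds its size, so this is a point about efficiency. The size of the gain depends on a correlation the article does not give. If N = 20 was derived for the four-visit interaction, ρ would be about 0.57 to 0.6, and at 1.155 SD the gain is then about 5 to 6 points and not 10. All of that stands, and it is why the range matters more than any single figure.

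Four stronger readings are tempting, and the documents do not support them.

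- A reader might infer that the ANOVA is biased. It is not: the shift is conditional on the imbalance observed and averages to zero over randomisations.
- Imbalance might be counted as a second harm. It is the same imprecision seen conditionally, already contained in the change-score standard error (0.365 SD at ρ = 0.5).
- One might say that nothing in the design limits baseline SRS imbalance. Stratification on comorbidity may do so in part if comorbidity tracks SRS severity, and the article does not say whether it does.
- The step from about 73% (planned interaction) to 95% at ρ = 0.5 might be credited wholly to adjustment. Part of it comes from replacing a 3-df test with a 1-df contrast. Only the 85% to 95% comparison isolates adjustment, and neither of those two contrasts is named in the article.

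That the article condenses a longer document is a weak defence, because the primary model is stated in full.

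**Conclusion.** The point holds as a recommendation on precision. The primary model treats baseline SRS as a response with no covariate, so its contrasts against baseline are unadjusted change scores. At the planned effect, adjustment is worth about 23 points of power at ρ = 0.3, 10 at 0.5, 5 at 0.6 and 2 at 0.7, and almost nothing at 0.8 or above, where power is already near 100%. At 0.8 SD it is worth about 12 points at ρ = 0.6 and about 2 at ρ = 0.8. These figures rest on compound symmetry, equal arms of 10, a sustained effect and the mean post-baseline contrast. They do not show that the planned test is invalid or that N = 20 is wrong. Because the baseline score is collected anyway, the improvement is worth making.

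**What to change.** In the Statistical Analysis section, take the pre level out of Time. Model the post, 1-month and 6-month caregiver SRS raw scores with Group, Time, Group × Time and baseline SRS as covariate, with a participant random effect and a small-sample degrees-of-freedom method. A constrained longitudinal model with one common baseline mean for both arms is an equivalent choice.

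The primary test must be restated at the same time. Once baseline leaves the Time factor, Group × Time tests only whether the effect differs between post-baseline visits and no longer tests efficacy. Name one baseline-adjusted active-minus-sham contrast instead, for example the average over the post-baseline visits or one pre-named visit. Keep the 4 × 2 ANOVA as a sensitivity analysis.

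The cost is one degree of freedom (included in the adjusted power figures above), a reworded primary hypothesis, and an update of the Sample Size Calculations section to match the new contrast and state the assumed correlation. No new data, visits or participants are needed. The Trial Status section describes the trial as ongoing, so the change should be dated and made before unblinded SRS data are examined.

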#### Exclusion Criteria

Contraindications for tDCS such as cardiac pacemakers, defibrillator, cochlear implant, intracranial/cranial stimulators, and other metals in the headContraindications for MRIEpilepsy or related seizure disordersOther severe neurologic or psychiatric disorders or medical conditions (e.g., skull defect and craniotomy)Concomitant psychopharmacological medication.

Ongoing concomitant social or psychotherapeutic long-term interventions must be held constant during the course of the intervention.

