## Trial Status

The described trial is ongoing, and recruitment commenced in July 2019. Recruitment and interventions had to be paused due to COVID-19 restrictions from March 13, 2020 to June 15, 2020. The data collection will continue until 20 participants completed all 10 intervention sessions and the corresponding pre- and post-measurements. Follow-ups will be conducted 1 and 6 months after the stimulation sessions to investigative long-lasting effects.

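### The primary question names no visit, and the 3-df time-by-group interaction chosen to test it cannot by itself show a reduction versus sham

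*Protocol article*

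**What the plan says.** The Outcomes section of the protocol article words the primary outcome with a direction: "The primary outcome will be a reduction in ASD symptoms from baseline in the experimental group compared to the sham group". The measure is the SRS raw score "assessed by the primary caregiver". No visit is attached to it.

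Statistical Analysis specifies a 4 × 2 mixed ANOVA for this outcome, with time ("pre vs. post vs. follow-up 1 vs. follow-up 2) as the within-subjects factor") crossed with group, which "will be conducted to investigate an interaction between time and group". For specific effects, post-hoc "tests will be employed". The contrasts are not listed. The general threshold is that p < "0.05 will be considered statistically significant".

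Elsewhere the follow-up visits serve a different purpose. The last paragraph of the Introduction lists long-term effects as a second, exploratory aim. The Discussion ties the follow-ups to persistence of effect. Trial Status says "Follow-ups will be conducted 1 and 6 months after the stimulation sessions to investigative long-lasting effects" and defines the target of 20 by completion of the sessions and the pre- and post-measurements. This hints that post-treatment is the main visit, but no section says so.

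**The concern.** The question and the test do not match. The question is whether active stimulation lowers SRS relative to sham. The interaction asks whether the two mean profiles over four visits are non-parallel in any way. Arms that separate only at 6 months, or an active arm that worsens, can make it significant.

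The claim of benefit therefore rests on the post-hoc step, where neither visit nor contrast is fixed. With 20 participants and one primary outcome, a decisive visit that can be picked after seeing the results weakens the main conclusion. The article itself selects this decision test, so the mismatch is not a detail left to a fuller document.

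**Working it through.** **Inputs.** N = 20, f = 0.25, power 80% and α = 0.05 (Sample Size Calculations); two groups and four visits (Statistical Analysis). Not stated and therefore assumed: 10 per arm (n = 10), equal correlation ρ between visits, equal SDs, sphericity.

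**1. The plan's own figure.** For a time-by-group interaction with m visits, λ = f²·N·m/(1 − ρ), df = (m − 1) and (N − 2)(m − 1).
- Four visits, ρ = 0.5: λ = 0.0625 × 20 × 4/0.5 = 10, df 3 and 54. Power is 72.7%, and 80% needs N = 24. N = 20 is reached only from ρ of about 0.58 (at ρ = 0.6, power is 82.7%).
- Pre and post only, ρ = 0.5: power is 56.2% at N = 20, and 80% needs N = 34. N = 20 requires ρ of about 0.72.

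So 20 can be matched under some correlations but not confirmed, and the statement does not show which effect or visit was powered.

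**2. What the interaction test responds to.** Let d_j be the active-versus-sham difference at visit j in SD units, positive meaning benefit. Then λ = (n/2)·Σ(d_j − d̄)²/(1 − ρ). With n = 10 and ρ = 0.5 this is 10·Σ(d_j − d̄)².

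| True pattern (pre, post, 1 month, 6 months) | Σ(d_j − d̄)² | λ | Power |
|---|---|---|---|
| Sustained benefit (0, 1, 1, 1) | 0.75 | 7.5 | 58.8% |
| Benefit at post only (0, 1, 0, 0) | 0.75 | 7.5 | 58.8% |
| Difference at 6 months only (0, 0, 0, 1) | 0.75 | 7.5 | 58.8% |
| Worsening on active (0, −1, −1, −1) | 0.75 | 7.5 | 58.8% |
| Fading benefit (0, 1, 2/3, 1/3) | 0.556 | 5.56 | 45.4% |

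The first four patterns mean quite different things clinically, and the F test cannot tell them apart.

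**3. What the post-hoc step adds.** Simulated trials with three change-from-baseline comparisons, each at 0.05:
- No effect at any visit, ρ 0.5 to 0.7: at least one false positive in about 13% of trials if the comparisons run regardless of F (1 − 0.95³ = 14.3% if independent), and about 4% if they run only after a significant F.
- True 1.0 SD effect at post only, ρ = 0.5, comparisons run only after a significant F: a false claim at 1 or 6 months in about 8% of trials. In about 9% the F is significant but no change-from-baseline comparison is.

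**4. Power of a single contrast at post-treatment.** For a difference D in SD units, the baseline-adjusted contrast has noncentrality D·√(n/2)/√(1 − ρ²) on 17 df. The plain change score has D·√(n/2)/√(2(1 − ρ)) on 18 df. Example at D = 0.8, ρ = 0.5: 0.8 × 2.236/0.866 = 2.07, and 0.8 × 2.236/1 = 1.79.

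| Pattern, D, ρ | Interaction | Change score at post | Baseline-adjusted at post |
|---|---|---|---|
| Sustained, 0.8, 0.5 | 40% | 40% | 50% |
| Sustained, 0.8, 0.7 | 62% | 59% | 66% |
| Sustained, 0.8, 0.8 | 81% | 76% | 80% |
| Fading, 1.0, 0.5 | 45% | 56% | 68% |

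For a sustained effect the whole gain comes from baseline adjustment, since the change score does no better than the interaction. For a fading effect, roughly half comes from concentrating on one visit (45% to 56%) and half from adjustment (56% to 68%).

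**The case against.** A time-by-group interaction is a common primary test in small repeated-measures trials. Direction can be read from the estimates, and a two-sided contrast is non-directional too. This is fair as far as it goes. But the sign of a single contrast at a named visit has one reading, whereas a significant 3-df F has no single estimate to take a sign from.

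Three stronger readings are tempting, and the documents do not support them:

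- **That the plan runs at about 13% family-wise error.** This assumes comparisons that are unadjusted and made whatever the F test shows. The article says neither, and an adjustment may sit in a document not shown. Under the global null with gating, the figure is about 4%.
- **That the interaction necessarily costs power.** Against a plain pre-post change score it loses nothing when the effect is sustained. Against the baseline-adjusted contrast the gap nearly closes at ρ = 0.7 and slightly reverses at 0.8. A baseline-adjusted mean of all three later visits would reach about 74% at 0.8 SD and ρ = 0.5, but that is a different endpoint from the one proposed here.
- **That the 6-month visit is biased because concomitant interventions "must be held constant during the course of the intervention" only.** The Blinding section keeps allocation concealed until after that visit or dropout, so therapy changes during follow-up would add noise. No differential bias is shown.

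**Conclusion.** The concern holds as a mismatch between question and test: no primary visit or contrast is named, and the stated decision test can be significant without any reduction versus sham. This part needs no assumption about effect size.

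The numerical consequences are moderate and conditional. With gated post-hoc tests and a 1.0 SD effect at post only, about 8% of trials make a false follow-up claim and about 9% end with a significant F and no identified difference from baseline. The power change from the remedy ranges from about +10 points (sustained 0.8 SD, ρ = 0.5) to −1 point (ρ = 0.8), and is about +23 points if a 1.0 SD effect fades at ρ = 0.5. All of this rests on 10 per arm, equal variances and a common correlation, none of which the article states. A reader should not infer a demonstrated loss of error control or a general loss of power.

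**What to change.** In Outcomes and Statistical Analysis, state: the primary endpoint is the baseline-adjusted active-minus-sham difference in caregiver SRS raw score at the post-treatment visit, tested two-sided at 0.05 as one contrast from a longitudinal model containing all visits, and reported with its 95% confidence interval. Make the 1- and 6-month differences secondary, as measures of persistence, tested in fixed order and only if the primary contrast is significant. Drop the omnibus interaction as the decision test; it can still be reported descriptively. Restate the sample-size justification for this contrast, with its assumed correlation.

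The cost is wording, agreed before the analysis data are unblinded; no new data are needed. The follow-up differences lose primary status, and the restated calculation may show less than 80% power at N = 20 for the effect the investigators have in mind.

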Another factor influencing social interactions is the direction of gaze (15). Eye-tracking reveals that children with ASD show aberrant patterns of gaze and fixation times when seeing human faces (16, 17) and eye gaze abnormalities have even been proposed as a robust biomarker for ASD (16). Moreover, dysfunctions in several brain regions including the dorsolateral prefrontal cortex (DLPFC) are involved in the development of this aberrant gaze behavior. In typically developing individuals, direct gaze leads to an enhanced response in brain areas important for empathic processes like theory of mind (ToM). In contrast, individuals with ASD show the same response when the gaze is averted and respond to direct gaze with an abnormal activation of the ToM network [medial prefrontal cortex (MPFC), temporoparietal junction, posterior superior temporal sulcus region, and amygdala] (15). These regions are also part of the social brain network (SBN) (18, 19).

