Research regarding the neural underpinnings of behavioral social problems in ASD found evidence for alterations within the SBN in structural and functional magnetic resonance imaging (MRI) studies (20). Furthermore, structural MRI studies showed abnormalities in gray matter volume and white matter structure in short-distance tracts in the SBN, as well as an association between these abnormalities and social malfunctioning in ASD (21–24). Task-related fMRI studies in individuals with ASD revealed atypical activity and connectivity in social brain regions during the processing of social stimuli (25). For instance, processing of emotional facial expressions was associated with reduced activity in several brain regions important for interpersonal interactions, including the amygdala, MPFC, ventrolateral prefrontal cortex, and superior temporal sulcus region in individuals with ASD compared with typically developing individuals (26). Neuroimaging results show that the most consistently activated brain regions in ToM tasks are the medial prefrontal and orbitofrontal cortices (27). Within the ToM network, reduced functional connectivity in persons with ASD was detected (15). In detail, the functional connectivity between the MPFC and the posterior cingulate cortex (PCC) has repeatedly been shown to be lower in individuals with ASD (28, 29). A weaker connectivity between these regions is correlated with more serious social impairments [see (29)]. Both the MPFC and the PCC are part of the default mode network (DMN), which is involved in complex emotional and social processes such as ToM and self-referential thoughts (30, 31). Functional connectivity of DMN regions has been shown to be altered at rest and reduced in several social tasks such as face processing in adolescents and adults with ASD (28, 32). While the functional connectivity between the DMN nodes normally increases with age, the development of long-distance functional connectivity in the DMN cannot be observed in adolescents with ASD (28, 33). Also, brain regions important for social interactions outside the DMN exhibit reduced activity and functional connectivity during resting state (20). Individuals with ASD showed, compared with typically developing individuals, a weaker functional connectivity between the amygdala and the ventromedial prefrontal cortex (34) and a reduced connectivity within the lateral occipital cortex, which was associated with symptom severity (35). Thus, it appears that neurophysiologically based interventions should target the MPFC as a potential mediator for the reduction of ASD symptoms.

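### The only stated seed source for resting-state fMRI is undefined regions of emotion-task activation, so the secondary outcome of connectivity within the ToM network and DMN is not specified to be tested

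*Protocol article*

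**What the plan says.** In the protocol article, the Outcomes section places the neurophysiological measures in the paragraph on secondary outcomes. They are taken at baseline and after the intervention, "using resting-state EEG and fMRI to measure changes in functional connectivity and electrical activity in the brain". The expectation stated there is "an increased connectivity within the ToM network and DMN".

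The Introduction says which regions these networks contain. It gives the ToM network as "medial prefrontal cortex (MPFC), temporoparietal junction, posterior superior temporal sulcus region, and amygdala". For the DMN it says "Both the MPFC and the PCC are part of the default mode network (DMN", and it reports that "the functional connectivity between the MPFC and the posterior cingulate cortex (PCC) has repeatedly been shown to be lower in individuals with ASD".

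The fMRI part of the Statistical Analysis section gives the method: "The RS data will be analyzed by means of seed-based functional connectivity". The seed rule is "Since the ERTs constitute newly implemented paradigms, interesting regions of their baseline activation will be used as seeds here". Time-by-treatment effects are then tested with family-wise error control at 0.05 at the peak level, alongside a cluster-level criterion.

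**The concern.** A seed-based analysis answers one kind of question: how the rest of the brain couples with the chosen seed. The choice of seed therefore decides which hypothesis is tested. The hypothesis here concerns two named networks, but the seed rule refers to neither. It takes regions that someone finds interesting in the activation map of a newly developed task, and it gives no criterion for that judgement.

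Two things are at stake. First, the trial could finish without having tested its own resting-state connectivity prediction, although that prediction is central to its neurobiological rationale. Second, the identity and number of the seeds stay open until trial data have been inspected. A positive result from one of them would then be hard to interpret as confirmation of a pre-stated secondary outcome.

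**Working it through.** No figure in the article depends on this point, so there is nothing to reproduce. The check is a comparison of sections, followed by a short illustration.

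**Step 1: outcome against seed rule.**

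| Element | Where | Content |
|---|---|---|
| Outcome | Outcomes | Rise in connectivity within ToM network and DMN, before to after intervention |
| ToM nodes | Introduction | MPFC, temporoparietal junction, posterior superior temporal sulcus region, amygdala |
| DMN nodes | Introduction | MPFC and PCC |
| Method | Statistical Analysis | Seed-based connectivity |
| Seed source | Statistical Analysis | Regions of ERT activation judged interesting |
| Number of seeds, selection criterion | Statistical Analysis | None given |

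No entry in the seed-source row guarantees any node in the two node rows.

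**Step 2: could the ERT supply the nodes anyway?** For some of them, yes. The Introduction links emotional face processing to the amygdala, MPFC and superior temporal sulcus region, all of which overlap the ToM list. It names neither PCC nor the temporoparietal junction in that sentence. The gap is therefore clearest for the DMN, where PCC is one of the two named nodes.

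**Step 3: does another planned analysis fill the gap?** EEG connectivity is planned, but the article does not define the ToM network or DMN for it. The Frith-Happé animations are a validated ToM task, but their outcome is regional activation, and they are not named as a seed source.

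**Step 4: the stated reason.** The rule is justified by the newness of the ERTs. That may be a reason to explore their activation. It does not connect the seeds to the two networks in the outcome.

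**Step 5: multiplicity, as illustration only.** Family-wise control at the peak level works within one seed map. If k maps were independent and each held at 0.05, the chance of at least one false-positive map would be 1 − 0.95^k:

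- k = 2: 1 − 0.95² = 0.098
- k = 5: 1 − 0.95⁵ = 0.226
- k = 10: 1 − 0.95¹⁰ = 0.401

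Both k and independence are assumptions. Correlated seeds would give lower values.

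**Step 6: what a fixed set would cost.** The distinct nodes named are MPFC (on both lists), PCC, temporoparietal junction, posterior superior temporal sulcus and amygdala, which makes five. A Bonferroni share is 0.05/5 = 0.01 per seed. If the last three were entered separately for each hemisphere (an assumption), the count would be 2 + 3 × 2 = 8, and the share 0.05/8 = 0.00625.

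**The case against.** The strongest reply has four parts.

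*The ERT is a reasonable source of seeds.* The intra-stimulation training, of which it is part, is meant to engage the targeted circuits, and its activation may well include ToM nodes. The sentence also does not say that no other seeds will be used. This stands in part. A reader might infer that the outcome will certainly go untested, and the document does not support that. It supports only that a test is not specified.

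*The choice need not be circular.* The word baseline can mean the fixation period within the task or the pre-intervention visit, and the article uses it in both senses. If it means the visit, seeds come from scans made before any stimulation and from a different acquisition than the resting-state data. Such a choice does not by itself favour a time-by-treatment effect. This stands: a reader might infer outcome-driven selection, but the text does not establish it. The undefined criterion remains under either meaning.

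*MPFC–PCC coupling is not the declared outcome.* It is background and earlier evidence in the Introduction, whereas the Outcomes section names the two networks. This stands too. Demanding a single MPFC–PCC contrast would narrow the stated outcome and would be a matter of preference.

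*An article leaves seed coordinates, seed number and correction across seeds to a fuller plan.* This is fair for those details, and their absence is not the finding. It does not answer the main point, because the seed source is stated outright, with a reason, and does not match the outcome it is meant to serve.

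**Conclusion.** The point holds as a mismatch between two statements in the current text. The Outcomes section commits to connectivity within the ToM network and DMN. The only seed source stated in the Statistical Analysis section does not ensure that a node of either network is examined, and it leaves the selection to an undefined judgement made after task data are available.

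The consequence is limited to one secondary outcome. The protocol already describes its secondary analyses as underpowered, so a null result would settle little with any choice of seeds. The SRS primary analysis does not depend on this.

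A reader might be tempted to attach a false-positive rate of 23% or 40% to the plan. Those values need 5 or 10 independent seeds, and the document gives neither a number nor grounds for independence, so the actual rate cannot be determined. The conclusion does not rest on them. It rests on reading the seed sentence as the operative rule for the resting-state analysis, which is how it is placed and worded.

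**What to change.** Before unblinding:

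1. Name the ToM and DMN nodes from the Introduction (MPFC, PCC, temporoparietal junction, posterior superior temporal sulcus, amygdala) as a priori seeds, with their definitions fixed, for the time-by-treatment test of the secondary connectivity outcome.
2. State one correction over that fixed set.
3. Keep ERT-derived seeds if wanted, but label them exploratory. Say which scan baseline refers to and what makes a region eligible.

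This takes a few lines of analysis text, with no new scans and no change to the primary analysis. The downside is the stricter threshold per seed in a trial of 20 participants. A less conservative correction that uses the correlation between seeds would soften this, provided it is also chosen in advance.
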